### Trial design

This is a multi-centre, double-blind, superiority RCT which takes place at 9 hospitals in 7 countries:the Sahlgrenska University Hospital in Gothenburg, Sweden; the Rizzoli Orthopaedic Institute in Bologna, Italy; the University of Alberta Hospital in Edmonton, Canada; Worker Hospital in Santiago, Chile; the NHS Lothian, NHS Clyde & Greater Glasgow, and NHS Grampian, UK; Dandenong Hospital, Monash Health in Melbourne, Australia; the Northwestern Memorial Hospital in Chicago, USA; the University of Michigan Health System in Ann Arbor, Michigan, USA; and within the Massachusetts General Hospital in Boston, USA. One hundred ten participants will be recruited and randomly assigned to one of three surgical treatments (TMR, RPNI, or neuroma transposition) in an equal allocation ratio (*n* = 37 per group). Each participant will be followed up short term (1, 3, 6, and 12 months post-surgery) and long term (2 and 4 years post-surgery). After the 12-month follow-up, the study will be unblinded for the evaluator and the participants. If the participants are unsatisfied with the outcome of the treatment, they may request one of the other treatments. In such a case, a medical evaluation and further treatment options will be discussed in consultation with the clinical investigator at the site. See the study flowchart in Fig. 2.

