#### Withdrawal or termination of individual participants

Participants can discontinue their participation in the study at any time, without any consequences on their clinical treatment at their respective hospitals or health care systems. The clinical investigator at the site can at any time terminate participation in the study for an individual if the participant’s safety can no longer be maintained due to any harmful clinical event, clinical anomalies, if other medical conditions or situations occur, or if the participant no longer fulfils the study criteria due to recently developed or not previously recognised disorders. Adverse events (AE) will be presented together with the results of the study.

We will employ the intention-to-treat (ITT) methodology in the analysis of the primary outcome. In case of non-adherence to the protocol, such as crossovers between surgical interventions after randomisation, the data will be analysed by grouping participants to their originally allocated intervention. Furthermore, the last collected data point will be used in the primary analysis in the case that data is missing due withdrawal, termination, or missed follow-ups. A sensitivity analysis of the primary analysis will be performed. A complementary analysis of the primary outcome will also be performed on the per-protocol (PP) population. The secondary outcomes will be analyses on both ITT and PP populations. Based on previous studies, drop-outs are expected to be around 10%.

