### Statistical analyses

The statistical analyses will be performed pairwise comparing the techniques in the following scheme:Reconstruction techniques compared to control: TMR and RPNI vs control (2:1)Individual comparison of each reconstruction technique compared to the control: TMR vs control (1:1) and RPNI vs control (1:1)Comparison between the reconstructive techniques: TMR vs RPNI (1:1)

Statistical analysis for the primary outcome, the mean difference of change in NRS score (0–10) of residual limb pain between baseline and 1-year follow-up between the two reconstructive surgical methods and control (2:1), will be performed with an ANCOVA for comparison of independent means on ITT population at 5% significance level, adjusted for the stratification (minimisation) variables NRS pain at baseline, level of amputation, and site. Imputation will be performed with the last observation carried forward (LOCF). A sensitivity analysis will be performed using a two-sided non-parametric permutation test for comparison of independent means on the ITT population. A complementary analysis will be performed for the primary variable of the PP population. The main results will be the mean difference with 95% CI, effect size, and *p*-value.

Secondary analyses will be performed unadjusted, between the two groups on both ITT and PP-population with Fisher’s non-parametric permutation tests for continuous variables, with the Mantel–Haenszel chi-square test for ordered categorical variables, and with Fisher’s exact test for dichotomous variables and performed adjusted with ANCOVA for continuous variables and with multivariable logistic regression for dichotomous variables.

Exploratory analyses will be performed to investigate the differences in groups such as lower vs upper extremity, right vs left extremity, female vs male, reason for amputation, baseline NRS (medium 4–6, high 7–10), time since amputation, and age. These exploratory analyses will be done within each group and then pooled together. All significance tests will be two-sided and conducted at the 5% significance level. When half of the study population has passed the 1-year follow-up, an independent committee including a medical expert and a statistician will examine the data with regard to safety.

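### LOCF as the primary imputation analyses an early post-operative or baseline score as 12-month pain, and the one sensitivity analysis specified changes the test, not that assumption

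*Protocol article*

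**What the plan says.** Two sections of the protocol article fix the rule. Under Statistical analyses, the primary comparison (both reconstructive techniques against control, 2:1) is an ANCOVA on the ITT population, and "Imputation will be performed with the last observation carried forward (LOCF"). Under Withdrawal or termination of individual participants, "the last collected data point will be used in the primary analysis" when data are missing through withdrawal, termination or a missed follow-up. No reason for choosing LOCF is given.

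The endpoint is the change in residual limb pain NRS from baseline (visits 0 to 3) to one year. Under Trial design, "Each participant will be followed up short term (1, 3, 6, and 12 months post-surgery"), so three post-operative scores are scheduled before the endpoint.

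On robustness, the withdrawal section says "A sensitivity analysis of the primary analysis will be performed", without describing it. Statistical analyses gives the content: "A sensitivity analysis will be performed using a two-sided non-parametric permutation test for comparison of independent means on the ITT population". It adds: "A complementary analysis will be performed for the primary variable of the PP population".

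On the expected amount of missing data: "Based on previous studies, drop-outs are expected to be around 10" per cent.

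**The concern.** LOCF treats the last recorded score as if it were the 12-month score, which is right only if pain does not change after that visit. The protocol gives reasons to doubt this. Its Background says that TMR and RPNI act by letting severed nerves grow into new target muscle, and its Interventions section describes the TMR denervation as temporary. The control does not denervate its muscle. Recovery may therefore take time and may follow a different course by arm. If it does, carrying early scores forward distorts the contrast even when drop-out is equal. If drop-out is unequal, the distortion can arise even with identical recovery curves.

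The direction is not known in advance. Scores carried from before full relief shrink that arm's improvement, and scores carried from a period of early relief that later fades inflate it. LOCF therefore cannot be defended as conservative. What is at stake is the primary estimate and its confidence interval, because no analysis described in this document shows how far they depend on the carried values.

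**Working it through.** **Inputs.** From Sample size: SD 2.2 (TMR, RPNI) and 3.3 (control), difference 2.0, two-sided 5%, power at least 80%, drop-out about 10%, 110 randomised. Assumed here, because the document does not give them: the true mean improvements, the split of drop-out between arms, and how much of the eventual change is present at the last visit.

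**The plan's own figures first.** Using a two-sample comparison with unequal SDs (Welch):
- 56 vs 28: SE = √(2.2²/56 + 3.3²/28) = 0.690, power 80.8%.
- 33 vs 33: SE = √(2.2²/33 + 3.3²/33) = 0.690, power 81.2%.
- A simulated permutation test gives about 87% and 81%. Drop-out: 99/0.9 = 110.

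The stated sample sizes are reproduced.

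**Effect of LOCF on the estimate.** Let R and C be the true mean improvements, pR and pC the drop-out proportions, and f the share of the eventual change present at the last observation. Then

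estimated difference = R(1 − pR + pR·f) − C(1 − pC + pC·f).

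*Equal drop-out, 10% in each arm, R − C = 2.0.* The formula reduces to 2.0 × (0.9 + 0.1f):
- f = 0 (baseline carried): 2.0 × 0.90 = 1.8
- f = 0.5 (half the change seen): 2.0 × 0.95 = 1.9
- f = 1.5 (early relief 1.5 times the lasting relief): 2.0 × 1.05 = 2.1

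*Unequal drop-out, about 10% overall at 2:1, R = 4, C = 2, f = 0:*
- 13% vs 4%: 4 × 0.87 − 2 × 0.96 = 3.48 − 1.92 = 1.56
- 5% vs 20%: 4 × 0.95 − 2 × 0.80 = 3.80 − 1.60 = 2.20
- 4% vs 22%: 4 × 0.96 − 2 × 0.78 = 3.84 − 1.56 = 2.28

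The shifts are −0.44, +0.20 and +0.28. With f = 0.5 the first and third halve, to 1.78 and 2.14.

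**Scale and power for the primary comparison.** With about 73 vs 37 analysed, SE = √(2.2²/73 + 3.3²/37) = 0.60, so a shift of 0.2 to 0.44 is about 0.3 to 0.7 of a standard error. At a difference of 1.8, Welch power is 84% with the planned SDs. If 10% of changes are exactly zero and the true improvements are 3 and 1, the SDs become √(0.9 × 2.2² + 0.09 × 3²) = 2.27 and √(0.9 × 3.3² + 0.09 × 1²) = 3.14, and power is 86%. For reference, 66 vs 33 completers with a difference of 2.0 give 87%.

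**Does a planned analysis vary the assumption?** The permutation test replaces the ANCOVA but uses the ITT population, for which LOCF is the only imputation stated. It would therefore carry the same bias. The per-protocol analysis changes the population, not the handling of missing 12-month scores within the ITT set.

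**The case against.** The strongest defence is that the effect is modest and the trial survives it. With equal drop-out the shift is 0.1 to 0.2 points, towards the null if relief is still incomplete, and the primary comparison stays above its power target. If the observed difference were 2.0 with SE 0.60, the lower confidence limit would be 2.0 − 1.96 × 0.60 = 0.82. Drop-outs making up 10% of the reconstructive arms would have to be 0.82/0.10 = 8.2 points worse than analysed to bring that limit to zero. All of this stands, and it limits the severity. It does not justify LOCF: the direction is not assured, and a result closer to the significance boundary would have less margin.

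It is also fair that this is a condensed article and the SAP is not shown. That the permutation test runs on LOCF-filled data is a strong inference, not a statement. The per-protocol analysis may exclude some non-completers, although that population is not defined here. A reader might infer that the assumption is never tested. The document supports only that no test of it is specified here.

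Four stronger readings are tempting and do not hold:
- *The standard error is about 5% too small, from √(1/0.9).* LOCF carries each participant's own score, and the ordinary SE describes that estimator properly. In simulation the empirical SDs were 0.581 and 0.602, against mean model SEs of 0.579 and 0.600. The problem is bias and what is being estimated.
- *Power falls from 81% to 77%.* That is TMR vs control, not the primary comparison, and it keeps the SDs unchanged. With the mixture SDs above it is 79%.
- *Type I error rises to 7.9%.* This needs 5% vs 20% drop-out and no follow-up score for any drop-out, despite visits at 1, 3 and 6 months.
- *An unblinded investigator can create the missing data.* The protocol does say "The clinical investigator at the site can at any time terminate participation in the study for an individual". But it lists grounds (safety, other medical conditions or situations, study criteria no longer met), requires an explanation for missing data, and does not say that termination ends outcome collection. The inference is speculative and is a separate matter.

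**Conclusion.** The concern holds as a should-fix. The document itself chooses LOCF for the primary analysis, in two places and without a reason, and the sensitivity analysis it specifies leaves that choice unexamined. At the planned 10% drop-out, a true difference of 2.0 would be estimated at about 1.8 to 2.1 with equal drop-out, and at 1.56 to 2.28 in the unequal scenarios worked above. These figures rest on assumed improvements, drop-out splits and recovery timing; they show the possible size and sign, not a forecast. The larger shifts need both unequal drop-out and baseline carried for every drop-out. The planned sample size is sound, and the primary comparison keeps more than 80% power in the equal drop-out case with baseline carried.

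**What to change.** Make the primary analysis valid under missing-at-random, by either of two routes:
- An MMRM on the 1-, 3-, 6- and 12-month residual limb pain NRS, with treatment by visit, baseline NRS and the minimisation factors, reporting the 12-month contrast.
- Multiple imputation by arm from the same visits, followed by the ANCOVA already stated. This gives results similar to the MMRM, not identical ones.

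Keep LOCF as a supportive analysis only. Add a delta-adjusted sensitivity analysis that makes the missing 12-month scores progressively worse, by arm, because missing-at-random cannot itself be verified. The permutation test can stay as a check on the test, described as such.

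The cost is wording in the two sections quoted and in the SAP, plus the programming of one model and one sensitivity analysis. All the visits are already scheduled and the target of 110 is unchanged. The change should be made before unblinding, since a later change to the primary missing-data rule would be hard to defend.

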##### Pain survey

The pain survey has 22 items based on the SF-MPQ [20] and study-specific questions. It is divided into five sections: residual limb pain, neuroma pain, phantom limb pain, general pain interference, and other questions. The survey evaluates the intensity, quality, and frequency of residual limb pain, neuroma pain, and phantom limb pain as follows:Numerical Rating Scale to evaluate the present intensity of pain (0–10 where 0 = no pain and 10 = worst imaginable pain).Present Pain Intensity Scale (range 0–5 calibrated as 0 = no pain, 1 = mild, 2 = discomforting, 3 = distressing, 4 = horrible, 5 = excruciating) [20].Pain quality is measured by SF-MPQ Pain Rating Index (PRI) by summing the 15 descriptions (range 0–3 calibrated as 0 = no pain, 1 = mild, 2 = moderate, 3 = severe) [20].Study-specific scale for evaluation of pain frequency (“constantly”, “few times per day”, “once a day”, “few times per week”, “once a week”, “few times per month”, “once a month”, “never”).

In addition, the phantom limb pain section monitors weighted pain distribution, phantom pain location, phantom telescoping, phantom sensation, and phantom motor ability [21].

The general pain interference questions track pain intrusion in daily activities, work, and sleep, using a numerical rating scale (0–10 where 0 = no interference and 10 = full interference) for each activity. Adjustment in prosthetic hardware and pain medication is also monitored in this section.

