##### EuroQoL-5D-5L (EQ-5D-5L)

The questionnaire EQ-5D-5L (EuroQol Group) is a standardised survey used to evaluate health-related quality of life, in terms of health status and health evaluation [23]. The health status is measured and evaluated in five categories: mobility, self-care, usual activities, pain/discomfort, and anxiety/depression. Each category is rated by a five-item scale (no problems, slight problems, moderate problems, severe problems, and extreme problems). The health evaluation part includes the EQ visual analogue scale (VAS) (0–100 where 0 = worst imaginable health state, 100 = best imaginable health state), and the participant is asked to rate their health that particular day.

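### Ordered categorical secondary outcomes, chiefly pain frequency, have no adjusted analysis although their baseline is collected, which gives up some precision

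*Protocol article*

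**What the plan says.** The Statistical analyses section of the protocol article sets out the secondary analyses by type of variable. The unadjusted set ("Secondary analyses will be performed unadjusted, between the two groups on both ITT and PP-population") covers three types: permutation tests for continuous variables, the Mantel-Haenszel "chi-square test for ordered categorical variables", and Fisher's exact test for dichotomous variables. The adjusted set covers two: it is "performed adjusted with ANCOVA for continuous variables and with multivariable logistic regression for dichotomous variables". No adjusted method is named for ordered variables. The primary ANCOVA, by contrast, is "adjusted for the stratification (minimisation) variables NRS pain at baseline, level of amputation, and site".

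The ordered outcome that the article lists explicitly is pain frequency. It is named under Secondary outcome measures and marked in Table 1 for all three pain types. The Pain survey section describes it ("Study-specific scale for evaluation of pain frequency") with eight options from constant pain to none. Table 3 places the pain survey at screening visit 0 and again at every follow-up visit, so each participant has a baseline category.

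**The concern.** Baseline pain frequency probably predicts pain frequency at 12 months. A comparison that leaves it out carries between-person variation that could be removed at no cost in data collection. The article adjusts the other two types of outcome, so the gap looks like an omission rather than a policy. At stake is the precision of three listed secondary comparisons, in a trial whose size was partly set by how few participants are available. The Mantel-Haenszel test by itself also yields no effect estimate or interval, so the reader would learn whether frequency differed but not by how much.

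**Working it through.** **Group sizes.** The Sample size section plans 33 evaluable participants per group, hence 66 versus 33 for pooled reconstruction against control and 33 versus 33 for single-technique comparisons. These sizes were set for the primary NRS outcome and they reproduce. With SDs of 2.2 and 3.3 and a difference of 2.0, Welch power is 80.8% at 56 versus 28 and 81.2% at 33 versus 33; 99/(1 − 0.10) = 110. The article states no power for ordered outcomes, so there is no figure of its own to reproduce here.

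**Assumptions.** The baseline-to-follow-up correlation ρ, the treatment shift and the spread over categories are not in the article. They are assumed: ρ from 0 to 0.7, a latent normal scale cut into equally likely levels, two-sided 5% tests.

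**Analytic guide.** Baseline adjustment multiplies the variance by (1 − ρ²). If the unadjusted test has 80% power, adjusted power is Φ((1.960 + 0.842)/√(1 − ρ²) − 1.960):

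- ρ = 0: 80%
- ρ = 0.3: Φ(2.802/0.954 − 1.960) = 84%
- ρ = 0.5: Φ(2.802/0.866 − 1.960) = 90%
- ρ = 0.7: Φ(2.802/0.714 − 1.960) = 97.5%

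This applies to the uncategorised scale. Grouping into levels loses part of the gain, so simulation is the better guide.

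**Simulation, eight levels, 66 versus 33, shift 0.6 SD.** The Mantel-Haenszel statistic is (N − 1)r², with r the correlation of category score and group. Its power was about 75% (75-78% across separate sets of runs). With the baseline score added, power was about 80% at ρ = 0.3, 82% at 0.5 and 89% at 0.6. Other runs of the same setting gave 85-86% at 0.5 and 90-92% at 0.6, so 82% and 89% are at the lower end.

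**Simulation, six levels, 500 runs per cell.** The shift was 0.62 SD at 2:1 and 0.72 SD at 1:1.

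| ρ | 66 v 33: MH on follow-up / MH on change / proportional odds | 33 v 33: the same |
|---|---|---|
| 0 | 75 / 44 / 75% | 80 / 47 / 81% |
| 0.3 | 79 / 63 / 83% | 79 / 60 / 81% |
| 0.5 | 81 / 73 / 88% | 80 / 74 / 88% |
| 0.7 | 75 / 90 / 95% | 76 / 87 / 95% |

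Power of the test on follow-up values does not depend on ρ, so its spread within a column is simulation noise (standard error about √(0.8 × 0.2/500) = 1.8 points). Using change scores is below the adjusted model in every row, and below the test on follow-up values up to ρ = 0.5.

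**Equivalent sample size at ρ = 0.5.** The ratio is ((1.96 + z_adj)/(1.96 + z_unadj))². For 75% to 82% it is ((1.96 + 0.915)/(1.96 + 0.674))² = 1.19. For 76% to 84.9% it is ((1.96 + 1.032)/(1.96 + 0.706))² = 1.26. The gain is worth about a fifth to a quarter more participants.

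**Type I error.** With the baseline score as the only covariate, null rejection was near 5%: 5.1% for a score-type test, and 5.8% for the proportional-odds likelihood-ratio test at 33 versus 33 (500 runs, standard error about 1 point). Adding amputation level and seven sites (2,200 runs, eight levels, ρ = 0.5, standard error about 0.5-0.6 points) gave 7.2% at 33 versus 33 and 7.5% at 66 versus 33. Entering baseline as separate categories as well gave 8.6% and 8.8%. Mantel-Haenszel gave 5.5% and 5.8%.

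**The case against.** The strongest reply is that nothing is stated wrongly. Mantel-Haenszel is a valid test for ordered data, randomisation protects its error rate, and a condensed article may leave an ordinal model to an analysis plan that is not shown. This stands in part: the issue is precision, not bias. But the article does specify methods type by type, and for this type it fixes a less efficient choice than for the other two.

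Several stronger readings are tempting and not supported:

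- *The baseline is discarded.* The article does not say whether the test is applied to follow-up values or to change from baseline. Change scores would use the baseline, though less efficiently than adjustment.
- *All ordered items are affected.* The "Present Pain Intensity Scale (range 0–5 calibrated as 0 = no pain") is described in the pain survey but not listed in Table 1. The EQ-5D-5L dimensions are nowhere said to be tested singly. PGIC is collected only after surgery and has no baseline. Pain frequency is the firm case.
- *One third more participants at ρ = 0.5.* That is 1/(1 − 0.25) = 1.33 on the uncategorised scale; the simulated powers give 1.19 to 1.26.
- *The same covariates as the primary model should be used.* The error rates above argue against it.
- *The trial's main conclusion is weakened.* The primary analysis is already adjusted, and the sample size does not rest on ordered outcomes.

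**Conclusion.** The point holds as a minor one. Ordered categorical is the only type of secondary outcome without a named adjusted analysis, and for pain frequency the baseline needed is already collected. Under the assumptions stated, the cost is nil at a correlation of 0, about 2 to 5 points of power at 0.3, roughly 7 to 10 points at 0.5 and about 14 points or more at 0.6. The article supplies neither the correlation nor the expected shift, so the size is conditional. No error in the primary analysis, the sample size or the validity of the stated test follows from this.

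**What to change.** Add one sentence to the Statistical analyses section: ordered categorical outcomes with a visit 0 value are also analysed on the ITT population with a proportional-odds model containing treatment and the baseline category of the same item as a linear score, reporting a common odds ratio with 95% CI. State that Mantel-Haenszel is the unadjusted companion, and whether it is applied to follow-up values or to change.

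Keep the covariates few. In particular, do not enter indicators for the seven sites in the 1:1 comparisons; the 66 versus 33 result suggests the same caution for the pooled comparison. PGIC can stay with the unadjusted test.

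The cost is small: standard software and no new data. Sparse neighbouring categories may need merging under a rule set before unblinding, and the proportional-odds assumption should be checked.

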### Assignment of intervention

#### Sample size

Sample size calculation is based on previous studies investigating the surgical treatments for neuroma pain [12, 13] and based on the limited number of available participants. To receive a minimum power of 80% from a Fisher’s non-parametric permutation test assuming a standard deviation of TMR and RPNI to be 2.2 and 3.3 for control [12] with a mean difference of 2.0 and at 5% significant level between the randomised groups in an allocation ratio of 2:1 (TMR and RPNI vs control), it is estimated that at least 84 (*n* = 28 per group) participants are required. With the same assumptions, but instead looking at one reconstruction technique compared to control in a ratio of 1:1 (TMR vs control, RPNI vs control), 99 participants (*n* = 33 per group) are needed to reach minimum power of 80% with a Fisher’s non-parametric permutation test with a mean difference of 2 NRS and at 5% significant level. The drop-out rate is expected to be around 10%; therefore, a total of 110 participants will be aimed to be randomised.

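### The exploratory factor analyses, run within each group and then pooled, cannot show whether the treatment effect differs between subgroups; a treatment-by-factor interaction should be added

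*Protocol article*

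**What the plan says.** The last paragraph of Statistical analyses in the protocol article introduces these analyses: "Exploratory analyses will be performed to investigate the differences in groups such as lower vs upper extremity, right vs left extremity, female vs male". It goes on to list cause of amputation, baseline NRS in two bands (4–6 and 7–10), time since amputation and age, which makes seven factors. The method follows in one sentence: "These exploratory analyses will be done within each group and then pooled together". The next sentence sets the level for every test: "All significance tests will be two-sided and conducted at the 5% significance level".

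The paragraph does not define 'group'. It names no treatment-by-factor term and no comparison of treatment effects across levels of a factor. The same section does plan an ANCOVA of the primary outcome on the ITT population, adjusted for baseline NRS, amputation level and site.

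**The concern.** In a three-arm superiority trial, a list such as limb level, sex and baseline pain is normally read as asking whether the operations work better in some patients than in others. That question needs the treatment difference in one subgroup set against the treatment difference in the other, with a standard error for the contrast. The stated method does not produce it under either reading of 'group':

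- **Group as treatment arm.** Lower and upper limb, say, are compared inside TMR, inside RPNI and inside control. This shows whether the factor predicts pain change. Pooling over arms then averages out any difference between arms.
- **Group as subgroup.** Treatment is compared with control separately in each subgroup. Pooling the subgroups returns the overall effect, so the only subgroup information left is one p-value beside another.

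With 5% tests attached, the output will include significant and non-significant results side by side, and these can differ often when the treatment effect is the same throughout. The choice of method is stated in the article, so this is not a detail left to an unseen analysis plan.

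**Working it through.** **Inputs from the protocol.** The Sample size section gives the SDs ("assuming a standard deviation of TMR and RPNI to be 2.2 and 3.3 for control") and the effect ("with a mean difference of 2.0 and at 5% significant level between the randomised groups"). It also gives 33 per group for the 1:1 comparisons, so 66 reconstructive versus 33 control, and 10% drop-out.

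**Assumptions.** The protocol gives no subgroup sizes, so splits of 50:50, 30:70 and 20:80 are used, the same in every arm. Outcomes are simulated as normal, without covariate adjustment.

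**1. The plan's own figures.** No figure is stated for the exploratory analyses. The sample size does reproduce: two-sided 5% unequal-variance t power is 80.8% for 56 versus 28 (stated total 84) and 81.2% for 33 versus 33 (stated total 99), and 99/0.9 = 110. These inputs are therefore a fair base.

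**2. Group as subgroup, same 2.0-point effect in both.** If the two tests have power p1 and p2, they disagree with probability p1(1 − p2) + p2(1 − p1). Pooled-variance t tests stand in for the permutation test:

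| Split | Sizes (treated v control) | p1, p2 | Disagreement |
|---|---|---|---|
| 50:50 | 33 v 17; 33 v 16 | 0.686, 0.675 | 0.686×0.325 + 0.675×0.314 = 43% |
| 30:70 | 46 v 23; 20 v 10 | 0.809, 0.485 | 0.809×0.515 + 0.485×0.191 = 51% |
| 20:80 | 53 v 26; 13 v 7 | 0.855, 0.361 | 0.855×0.639 + 0.361×0.145 = 60% |

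Welch tests give about 48–50%, 56% and 64%. An unequal-variance interaction test on the same data rejects in about 5–6%, close to its nominal level.

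**3. Group as arm, no effect modification.** With 33 per arm split about evenly, take a factor that shifts pain change by the same amount in every arm. It is significant in some arms but not all in the following share of trials:

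| Shift (NRS) | 0 | 0.5 | 1.0 | 1.5 | 2.0 | 3.0 |
|---|---|---|---|---|---|---|
| Arms disagree | 14% | 24–25% | 49–50% | 73–74% | 75–76% | 33% |

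The protocol supports no particular shift, so only the range is informative.

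**4. Group as arm, real effect modification.** Let the lower-versus-upper difference be +2/3 in TMR, +2/3 in RPNI and −4/3 in control. The interaction is 2/3 − (−4/3) = 2 points, and the three differences sum to zero. The pooled test rejects in 5% of trials, its false-positive rate; an interaction test rejects in 35%.

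**5. What an interaction test can deliver.** For a subgroup share f, Var = (2.2²/66 + 3.3²/33) × [1/f + 1/(1 − f)] = 0.4033 × [1/f + 1/(1 − f)]. Power for a 2-point interaction is about Φ(2/SE − 1.96), and the interaction detectable with 80% power is about 2.80 × SE.

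| Split | SE | Power, 2 points | Detectable at 80% |
|---|---|---|---|
| 50:50 | 1.27 | 35% | 3.6 |
| 30:70 | 1.39 | 30% | 3.9 |
| 20:80 | 1.59 | 24% | 4.4 |

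**6. Why unequal variances matter.** A common-variance model would use about (66×2.2² + 33×3.3²)/99 = 6.86. In place of 0.4033 it gives 6.86 × (1/66 + 1/33) = 0.312. The SE is then too small by a factor √(0.312/0.4033) = 0.88, and the nominal 5% test has a true level of about 2[1 − Φ(1.96 × 0.88)] = 8–9%.

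**The case against.** The strongest reply is that the article never says it is looking for effect modification. Its stated aim is only "Exploratory analyses will be performed to investigate the differences in groups such as lower vs upper extremity" and the like. If the question is prognostic, comparing factor levels within each arm and then pooling is coherent, and losing the treatment contrast is intended. This stands in part: the plan may be sound for prognosis. It should then say so, because the present text leaves both the question and the meaning of 'group' open.

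The analyses are also labelled exploratory. The label limits how strongly a result may be claimed; it does not change what the method estimates.

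Three stronger readings are tempting and not supported:

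- A reader might infer that the trial will announce that an operation works in one subgroup and not in another, or that these results will guide patient selection. The article plans no subgroup claim, no decision rule and no such use. Misreading is a risk, not a stated intention.
- A reader might take one figure from step 3, such as 74% at a 1.5-point shift, as the size of the problem. That value lies near the peak of a range from 14% to 76%.
- Seven factors in three arms make 21 tests, with 1 − 0.95²¹ = 66% chance of at least one false positive if independent. A reader might blame this on the missing interaction. It is ordinary multiplicity: seven interaction tests would still carry 1 − 0.95⁷ = 30%.

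**Conclusion.** The point holds as a defect of the stated exploratory method. Under either meaning of 'group', the plan does not estimate whether the treatment effect differs between subgroups. When the effect is in truth uniform at 2.0 points, within-subgroup tests disagree in about 43–64% of trials, against 5–6% false positives for an unequal-variance interaction test. Those figures rest on the protocol's SDs, 66 versus 33 evaluable, normal outcomes, assumed splits of 50:50 to 20:80, and the choice between pooled-variance and Welch tests.

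The change should be made, but the reach of the point is limited. It does not touch the primary analysis or the sample size, and it does not show that the within-arm and pooled analyses are wrong for a prognostic question.

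**What to change.** Define 'group' and add to the exploratory paragraph:

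> For each factor, a treatment-by-factor interaction will be added to the primary ITT ANCOVA, with standard errors that allow unequal variances. Treatment differences by subgroup will be reported with 95% CIs and the interaction p-value, as descriptive results without multiplicity control. Within-arm or within-subgroup significance will not be used to claim that the treatment effect differs.

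Label any within-arm and pooled analysis that is kept as prognostic. The prespecified baseline NRS bands may stay; a continuous version is optional.

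The cost is a few sentences and a few lines of code, with no new data. The downside is the low power shown in step 5, so a non-significant interaction must not be read as evidence that the effect is uniform.
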